### Criteria for discontinuation

There are two levels of discontinuation for participants in the ThrIVe-B arm: A participant may discontinue therapy but remain in the trial, or they may discontinue the trial. If a participant in either arm indicates at any point that they wish to discontinue the trial they will not be contacted further by the research team, other than to invite them to take part in a brief written survey to ascertain their reasons for not taking part. If a participant does not attend more than three consecutive group therapy sessions this will generally be judged to indicate discontinuation of therapy, as will the participant opting to discontinue at any point.

Individual participants will be discontinued from the trial if they experience a serious adverse reaction that is judged to be the direct result of the intervention or trial participation, or if the participant, the therapist, or the research team believes that the intervention or trial participation will result in, or is likely to result in, a serious adverse reaction if continued.

Should an unexpected serious adverse reaction occur to either the therapy or the trial procedures, and if this is judged to be directly related to trial participation or to the therapy, the trial will be temporarily halted pending investigation and analysis of the extent to which future risk can be mitigated. If it is judged that this is not possible, the trial will be discontinued. This process will be led by the sponsor in collaboration with the TSC chair and chief investigator. The same process will be followed should information come to light that indicates that the therapy intervention or trial procedures are unsafe.

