### Data analysis

#### Quantitative data analysis

Patients’ demographic characteristics at baseline will be reported by treatment group. The primary analyses will be performed after 9-month follow-up and after data cleaning is completed and the database finalised. Further analyses will be performed after the final 15-month follow-up. No interim analyses are planned.

All analyses will be done on an intention-to-treat basis; included outcomes will be reported according to randomised allocation and regardless of the treatment actually received. There will be no possibility of participants allocated to the control arm receiving the intervention; it is possible that participants allocated to the intervention will in actuality receive none of the intervention or will not complete the intervention (defined as attendance of at least 50% of group sessions). All outcomes will be reported descriptively. At 9-month follow-up only, an inferential analysis will be performed for continuous outcomes only, reporting the relevant 95% CI for the between-group mean difference (intervention minus TAU), but no *p* value. Inferential analyses will include the randomisation covariates: site and baseline medication status. No interactions between intervention status and covariates are planned.

Proportions of participants recruited (of those approached) and those lost to follow-up at 3, 6, 9 and 15 months, will be reported with 95% CIs. All analyses will use complete case data only. No attempts to address missing data, such as multiple imputation, will be made.

The economic analysis will take the NHS and social care perspective. No covariate analysis or subanalysis will be conducted, because this is a feasibility trial and is not powered for such inferential analyses. Descriptive data for each arm will be reported with CIs for between-group comparisons. No *p* values will be reported.

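### A serious adverse reaction to the therapy leads to discontinuation from the trial, not only from therapy, and nothing provides for continued outcome data in the intention-to-treat analysis

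*Protocol article*

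**What the plan says.** The Criteria for discontinuation section of the protocol article first describes two levels for the intervention arm: "A participant may discontinue therapy but remain in the trial, or they may discontinue the trial". For serious adverse reactions it then uses the second level: "Individual participants will be discontinued from the trial if they experience a serious adverse reaction that is judged to be the direct result". The cause may be the therapy or participation in the trial. The rule also has an anticipatory limb: "or if the participant, the therapist, or the research team believes that the intervention or trial participation will result in". The object is again a serious adverse reaction, and a belief that one is likely is enough.

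For people who themselves ask to leave the trial, the same section says that "they will not be contacted further by the research team, other than to invite them to take part in a brief written survey" about their reasons. It does not say what data collection, if any, follows a discontinuation on safety grounds.

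The Quantitative data analysis section says: "All analyses will be done on an intention-to-treat basis; included outcomes will be reported according to randomised allocation and regardless of the treatment actually received". It also says "All analyses will use complete case data only" and "No attempts to address missing data, such as multiple imputation, will be made".

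Two other places limit the point. Under Adverse events, every serious event related to the trial or the treatment is recorded and reported at once to the chief investigator and the sponsor, and symptoms of the bipolar or cyclothymic disorder itself do not count as adverse events. Under Objectives, the first continuation criterion turns on whether an unexpected serious adverse reaction occurs, and the third on 9-month data being available for at least 60% of all participants.

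**The concern.** The protocol has a level at which therapy stops and follow-up continues, but it does not use that level for reactions to the therapy. Whether a participant leaves the data would then depend on how that participant fared after randomisation.

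The loss would also be unequal between arms. The rule can reach the control arm through its reference to trial participation. However, only the intervention arm is exposed to the therapy, and only that arm has a therapist who can trigger the anticipatory limb.

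Three outputs are exposed: the 9-month confidence interval for the mean difference, the SDs meant to inform the sample size of a definitive trial, and the attrition estimate, in which a removal required by the protocol would be mixed with voluntary loss. A complete-case analysis does nothing to repair any of these.

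**Working it through.** **The plan's own figure.** The Sample size section gives 48 participants (24 per group), expected attrition of 17% at 9 months, and a precision of ±15% with 95% certainty. The half-width is 1.96 × √(p(1 − p)/n) with p = 0.17:

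- n = 24: 1.96 × √(0.17 × 0.83/24) = 0.150, or ±15.0 points.
- n = 48: 1.96 × √(0.17 × 0.83/48) = 0.106, or ±10.6 points.

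The stated figure reproduces with one arm's n and is conservative for the whole sample. It is not in dispute; it supplies the 24 and the 17% used below.

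**Reading the rules together.**

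1. A reaction attributed to the intervention leads to discontinuation from the trial, although a therapy-only level exists.
2. No section provides for outcome assessments after that step.
3. If assessments stop before 9 months, the participant has no 9-month score.
4. With complete cases only and no handling of missing data, a participant without a score is absent from the confidence interval and from the SDs.
5. Reporting regardless of treatment received then cannot be achieved for exactly those who stopped treatment because of harm.

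Step 3 is an inference from the words of the rule. The no-contact sentence is written for people who ask to leave.

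**Illustrative shift in the intervention mean.** If k of m would-be completers are removed, and each would have scored d SD worse than the rest, the arm mean moves in favour of the intervention by k × d/m. Here m = 24 × 0.83 = 19.9, about 20. The documents give neither k nor d, so both are assumptions.

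| Removed (k) | d = 1 | d = 2 | d = 3 |
|---|---|---|---|
| 1 | 0.05 SD | 0.10 SD | 0.15 SD |
| 2 | 0.10 SD | 0.20 SD | 0.30 SD |
| 3 | 0.15 SD | 0.30 SD | 0.45 SD |

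For scale, the half-width of the 95% confidence interval for the mean difference with 20 per arm is 1.96 × √(2/20) = 0.62 SD, before any covariate adjustment.

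**Illustrative effect on the SD.** Take the SD of the remaining completers as 1. With a fraction k/m lying d = 2 SD away, the full arm has variance 1 + (k/m)(1 − k/m)d².

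- k = 1: 1 + 0.05 × 0.95 × 4 = 1.19, SD 1.09.
- k = 2: 1 + 0.10 × 0.90 × 4 = 1.36, SD 1.17.

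The SD left in the data (1.00) would be smaller than that of the arm as randomised.

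**Effect on the 60% criterion.** It is counted over all participants, so each removal costs 1/48 = 2.1 points. Meeting it needs 0.60 × 48 = 28.8, so 29 people. At 17% attrition, 48 × 0.83 = 39.8, about 40, are expected. The margin is about 11 people.

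**The case against.** Several counterarguments have force.

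- **The event is not lost.** A reader might infer that the worst outcomes vanish from the trial, or that the safety criterion is undermined. The documents do not support this. Related serious events are recorded and reported, an unexpected related reaction halts the trial pending investigation, and the steering committee reviews adverse events. The first continuation criterion needs the occurrence of the event, not later scores. This stands.
- **Ordinary worsening does not trigger the rule.** Disorder symptoms are not adverse events, and the reaction must be judged a direct result or be expected. Poor mood scores alone stay in the data, so cases are probably few. The open trial of the programme saw no unexpected serious adverse reactions, though it had only 12 participants. This stands.
- **The end of follow-up is inferred.** The article is condensed, and the full protocol may say more. This stands as a caution. But the rule that sends these participants out of the trial is stated rather than omitted, and the article has a level that would keep them in.
- **Intention to treat is qualified.** The article openly says complete cases only, and nobody is reallocated. That is fair for ordinary attrition. It does not cover a rule of the protocol's own making that creates outcome-related missing data mainly in one arm.
- **Little turns on the 9-month contrast.** It carries no p value and no continuation criterion uses it. This limits the weight of the point. The SD and attrition estimates, however, are stated objectives.

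A reader might also infer that the 9-month result is biased as a matter of fact, or that each removal costs 1/24 = 4.2 points of the retention criterion. The first holds only if such cases occur before 9 months and would have scored worse. The second uses one arm as the denominator, whereas the criterion uses all 48.

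**Conclusion.** The point holds in a limited form. The discontinuation rule and the intention-to-treat statement do not fit together: participants with a reaction attributed to the intervention, or thought likely to have one, leave the trial, nothing in the article keeps their outcomes, and the complete-case analysis then drops them. Any such loss would be outcome-related and would fall mostly on the intervention arm.

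The size is conditional. With 1 or 2 removals among about 20 completers and outcomes 2 SD worse, the intervention mean would look better by 0.10 or 0.20 SD. That is well inside a confidence interval half-width of about 0.62 SD, but in a consistent direction. The number of removals and the 2 SD are assumptions, and the calculation takes it that outcome assessments do stop. The safety criterion is unaffected, and one or two removals could not plausibly decide the 60% criterion. It is worth correcting because the remedy is cheap and because a definitive trial could inherit the rule.

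**What to change.** Reconcile the Criteria for discontinuation and Quantitative data analysis sections by separating the safety decision from data collection. Leave the safety decision, including whether and when therapy stops, exactly as it is. Add that participants discontinued for a reaction attributed to the intervention are still invited, with their consent, to the scheduled 3-, 6-, 9- and 15-month outcome and safety assessments, unless the assessments themselves are judged to be the cause. State that they are analysed as randomised. Report any removals under this rule by arm, separately from other attrition.

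The cost is a wording amendment with the usual approvals and a few assessments that are already scheduled. The Trial status section describes recruitment as closed and follow-up as still to run, so the change could apply to the remaining visits and be carried into the definitive protocol.

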### Patient and public involvement

We developed the ThrIVe-B programme with input from the patient and public involvement (PPI) group at the University of Exeter Mood Disorders Centre (Lived Experience Group [LEG]), who advised on the content and form of the intervention. We then gathered detailed feedback from participants as part of our open trial of the programme. This feedback led to changes to the intervention in terms of both content and delivery, resulting in the intervention to be evaluated in the current study. This feedback also shaped the trial procedures we propose for this study. Our open trial also included obtaining feedback from referring NHS clinicians both before and after intervention delivery.

Our current trial protocol was developed with input from two members of the LEG. The ThrIVe-B trial team includes a PPI lead. With the chief investigator, this individual has convened and chairs a PPI reference group who oversee PPI strategy and operation for the trial. They also edit participant-facing research and therapy materials, consult on the conduct of the trial, and contribute to the dissemination strategy. We follow national good practice with regard to remuneration of PPI representatives.

### Trial governance

A trial steering committee (TSC), independent from the sponsor, has been convened, including independent members (academic and clinical) as well as the principal investigator and trial statistician, and will meet approximately five times over the life of the project. The TSC will be responsible for advising the trial team on the conduct of the study. Given the relatively small scale of the trial a separate data monitoring and ethics committee (DMEC) will not be convened. Instead the DMEC functions (reviewing data collected including adverse events and making recommendations for the future conduct of the trial) are included within the terms of reference of the TSC. For all substantive changes to the protocol approval will be sought from the sponsor and the relevant national regulatory bodies.

### Role of the funder and sponsor

The sponsor has ultimate authority over the management of the study. Neither the funder nor the sponsor of the study was involved in the design of the study and will not be involved in the collection, analysis or interpretation of data or the writing of the study report. The funder will be required to approve the final report prior to publication.

### Dissemination

Findings will be disseminated both at a local level, to participants, services and other stakeholders, and at a national/international level through conference presentations and publication of findings in a peer-reviewed journal in open access form. Findings will also be disseminated through media and social media where possible. The dissemination strategy will be informed by the trial PPI reference group.

## Discussion

This trial is designed to assess the feasibility and acceptability of a randomised controlled trial of a DBT-informed psychological intervention for individuals with BPMI in primary care. The findings will inform future investigation of this approach, potentially in the form of a definitive randomised controlled trial testing its clinical effectiveness and cost-effectiveness.

### Trial status

The start date of the trial was 6 June 2017. Recruitment ran from July 2017 to July 2018. Follow-up will last 15 months, with the entire study period lasting 29 months.

## Abbreviations

ALS: Affective Lability Scale
App: Smartphone application
BD: Bipolar disorder
BPMI: Bipolar mood instability
DBT: Dialectical behaviour therapy
DMEC: Data monitoring and ethics committee
DSM-V: *Diagnostic and Statistical Manual of Mental Disorders, Fifth Edition*
EQ-5D-5L: EuroQoL 5-Dimension 5-Level instrument
GP: General practitioner
LEG: Lived Experience Group
MRC: Medical Research Council
NHS: UK National Health Service
NIHR: National Institute for Health Research
PPI: Patient and public involvement
TAU: Treatment as usual
ThrIVe-B: Therapy for Inter-episode mood Variability in Bipolar
TSC: Trial steering committee
